### Data analysis

Analyses will be performed using Stata version 12 or later, and the ‘intention-to-treat’ principle will be adhered to. Baseline characteristics will be compared between intervention and control groups using chi-square tests, independent t-tests, and the Wilcoxon rank-sum test as appropriate. Primary and secondary outcomes (as described above) will be evaluated using mixed models, treating ‘group’ as a between-subject factor and ‘time’ as a within-subject factor. Two-sided tests will be used, with a level of *P* <0.05 determining statistical significance.

A separate and parallel economic evaluation protocol will be described elsewhere.

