### Outcome assessments

#### Primary outcomes

The primary outcomes under investigation are changes in diabetes and CVD risk as determined by changes in weight, waist circumference, fasting plasma and two-hour glucose, blood pressure and lipids. These are determined through anthropometric and laboratory measurements (performed as detailed below) at baseline, following the fourth group session (approximately three months after the commencement of the intervention) and 12 months after commencement of the intervention. The reduction in diabetes risk is calculated from the reduction in weight and waist circumference
[12] and the reduction in cardiovascular risk from changes to the Framingham risk score, which incorporates the changes in the individual risk factors.

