### Sample size and power calculation

For the estimation of sample size for two groups, with a two-sided 5% significance level and 80% power, the total number required will be 598 (299 in each arm). The sample size calculation was based on the observed mean change in diastolic blood pressure, a CVD risk factor, in the GGT-DPP and powered to detect an effect size of at least 0.23. To allow for an estimated attrition of up to 25% (estimate based on the GGT DPP), we require a total sample of 796 (398 in each arm). This sample size will provide sufficient power for other CVD risk factors, such as total and high-density lipoprotein (HDL)-cholesterol, as well as diabetes risk factors including fasting plasma glucose, weight, and waist circumference, as these are all expected to have larger effect sizes.

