### Randomization

Randomization to either the intervention or usual care arm is made after confirmation of the eligibility of the patient, and after exclusion of T2DM, based on the baseline clinical test results (both FPG <7 mmol/L and OGTT two-hour glucose <11.1 mmol/L). Randomization is generated by a random number table and participant instructions are placed in individual sealed, opaque envelopes. The Project Coordinator selects the next sequential envelope to be attributed to a new participant. A covering letter is sent to participants indicating which group (Intervention or Control) they are allocated to, and what the subsequent processes are for participating in the study.

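### The mixed models name no baseline adjustment, so the 12-month comparison reads as an unadjusted difference in change: unbiased, but less precise than the collected data allow

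*Protocol article*

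**What the plan says.** The Data analysis section states that primary and secondary outcomes "will be evaluated using mixed models", with group as the factor that differs between participants and time as the factor that differs within them. It names no baseline covariate and no common baseline mean, and it does not write out the contrast that estimates the treatment effect.

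Three other places bear on how that sentence is read:

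- Primary outcomes: "The primary outcomes under investigation are changes in diabetes and CVD risk", determined from changes in weight, waist, glucose, blood pressure and lipids.
- Study design, and Anthropometric measurements and laboratory testing: the intervention arm is tested at baseline, about three months and 12 months; the control arm at baseline and 12 months only.
- Randomization: "Randomization to either the intervention or usual care arm is made after confirmation of the eligibility of the patient", using the baseline glucose results. Baseline values therefore precede allocation.

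**The concern.** A control participant has two measurements. Time can vary within that participant only if baseline is one of its levels. So the stated model, read naturally, treats baseline as an outcome. If instead the analysed outcome were the change itself, each control would have a single value and time could not be a within-participant factor; that analysis would also be an unadjusted comparison of changes.

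With a free baseline mean in each arm, the model estimates a baseline difference that randomisation has already set to zero in expectation, and subtracts it at full weight. When r is below 1, the best weight for the baseline difference is r (with equal SDs), not 1. The excess weight adds noise to every continuous primary and secondary comparison. What is at stake is the width of the confidence intervals and the power, using data the trial already collects.

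**Working it through.** **Inputs from the article** (Sample size and power calculation): the trial is planned "with a two-sided 5% significance level and 80% power"; it is "powered to detect an effect size of at least 0.23"; the calculation is "based on the observed mean change in diastolic blood pressure"; 299 evaluable per arm; 25% attrition; 398 recruited per arm. The article does not say which SD standardises 0.23.

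**Assumed, not in the article:** the correlation r between baseline and 12 months, and equal SDs at the two times.

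**Step 1. Reproduce the plan's figure.** n per arm = 2(1.96 + 0.8416)² / 0.23² = 297, against 299 stated. Power at 299 per arm = Φ(0.23 × √(299/2) − 1.96) = Φ(2.812 − 1.96) = 80.3%. Inflation: 299/0.75 = 398.7, against 398 stated. The figures agree within rounding.

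**Step 2. Complete data.** With unit variance, the per-person variance is 2(1 − r) for a change and 1 − r² after baseline adjustment. The ratio is (1 − r²) / [2(1 − r)] = (1 + r)/2, so adjustment cuts the variance by (1 − r)/2. A generalised least squares calculation with group-by-time means confirmed that the free-baseline model has exactly the variance of the difference in change, and that a common baseline mean gives this cut.

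| r (assumed) | Variance cut | Standard error cut |
|---|---|---|
| 0.3 | 35% | 19% |
| 0.5 | 25% | 13% |
| 0.7 | 15% | 8% |
| 0.8 | 10% | 5% |
| 0.9 | 5% | 2.5% |
| 0.95 | 2.5% | 1.3% |

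**Step 3. Power, if 0.23 is in units of the SD of change.** Power = Φ(2.812/√[(1 + r)/2] − 1.96), and the required n is 296.7 × (1 + r)/2.

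| r (assumed) | Power at 299 per arm | n per arm for 80% |
|---|---|---|
| no adjustment | 80.3% | 297 |
| 0.5 | 90.1% | 223 |
| 0.8 | 84.2% | 268 |
| 0.9 | 82.3% | 282 |

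**Step 4. With the planned attrition.** Let p = 0.75 be the share with a 12-month value, missing at random, and N = 398 per arm. Leaving out the 3-month visit, the free-baseline mixed model has variance 2[(1 − r²)/(pN) + (1 − r)²/N], and the common-baseline model has 2(1 − r²)/(pN). The cut is p(1 − r) / [(1 + r) + p(1 − r)] = 20.0%, 7.7% and 3.8% at r = 0.5, 0.8 and 0.9.

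Adding the intervention arm's 3-month visit (attended by everyone in that arm, equal correlation r between all visits) gives:

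| r | Completers' difference in change | Free-baseline mixed model | Common baseline mean | Cut, free to common |
|---|---|---|---|---|
| 0.5 | 0.00670 | 0.00621 | 0.00496 | 20.2% |
| 0.8 | 0.00268 | 0.00255 | 0.00235 | 7.9% |
| 0.9 | 0.00134 | 0.00129 | 0.00124 | 3.9% |

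With dropout, the free-baseline mixed model is no longer the simple difference in change, because dropouts' earlier values still contribute, and the gain from adjustment is smaller.

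**Step 5. Completer-only ANCOVA.** Its variance is 2(1 − r²)/(298.5) = 0.00503, 0.00241 and 0.00127 at the same r. The common-baseline mixed model is 1.4%, 2.5% and 2.8% lower, because it keeps the 3-month values of those who miss 12 months.

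**The case against.** The strongest reply is that the article does not write out the model being criticised. It does not say that baseline means are free, gives no target contrast, and neither lists nor excludes covariates. A constrained longitudinal model is itself a mixed model with group between and time within participants, so the proposed remedy fits the stated sentence, and the full analysis plan may already contain it. This stands in part: the article cannot be said to rule adjustment out. But it does describe a concrete model, the visit schedule makes baseline an outcome level, and no adjustment is named. Making the choice explicit improves the plan whichever version was intended.

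A second reply is that the planned power may not need adjustment. That also stands. The sample size rests on a mean change, and if 0.23 is in units of the SD of change, 80.3% is reached without adjustment.

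Readers might also infer more than the documents support:

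- That the result would be biased, or spoiled by regression to the mean. Under randomisation the difference in change is unbiased. A chance baseline imbalance matters only conditionally on its having occurred.
- That a loss of 10% to 25% is a property of this trial. Those figures need r between 0.8 and 0.5, equal SDs and complete data, and the article gives no correlation. At r of 0.9 or more the cut is 5% or less, and attrition shrinks it further.
- That slow recruitment (266 randomised of 796 by 15 November 2012, in Trial status) makes the model wrong. It makes precision more valuable, but it is a separate matter.

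**Conclusion.** The point holds as a matter of efficiency, not validity. On the natural reading, the 12-month contrast does not use the equality of baseline means that randomisation after baseline testing provides, so it is less precise than it could be for any r below 1. With equal SDs and complete data, adjustment cuts the variance by 25%, 10% or 5% at r = 0.5, 0.8 or 0.9. With 25% of 12-month values missing at random, the cuts are about 20%, 8% and 4%. The correlation is assumed throughout and will differ between outcomes; those that track strongly within a person gain least. The documents do not show that the planned comparison is biased, that the stated 80% power fails, or that adjustment has been excluded. This is a free improvement.

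**What to change.** Keep the mixed model and add a sentence to the analysis section: both arms share one baseline mean, the 12-month means are free in each arm, the 3-month mean is estimated in the intervention arm only, and the treatment effect is the adjusted 12-month between-group difference, reported with its 95% CI for each continuous outcome. A near-equivalent form removes baseline from the outcome levels and enters it as a covariate.

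The constrained mixed model is preferable to ANCOVA on completers because it retains partial data from participants who miss 12 months, which also sits better with the stated intention-to-treat principle. The precision advantage over completer ANCOVA is small (1.4% to 2.8% of the variance in the cases above).

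The cost is the wording. No new data, visits or participants are needed. The adjustment should be fixed before outcome data are compared between arms, so that it does not depend on the baseline significance tests planned in the same section.

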## Discussion

This study is necessary because it is important to know if this specific modification of the Life! diabetes prevention program leads to a reduction in diabetes risk, whether this reduction is larger than the effect of usual care and how these two options compare economically. Information about the characteristics of participants that predict completion of the program and improvement in clinical and behavioral measures will be useful for further development of diabetes prevention programs. Translating clinical trials into effective population programs is very challenging, but this translational process can be successful. We expect that MDPS will confirm the effectiveness of Life! and may allow us to refine it further.

The links to health policy are immediate: the COAG has on its agenda the prevention of progression to diabetes among those at high risk. The results of this study, including economic evaluation information, will inform policy and future guidelines and will complement the European recommendations for prevention of T2DM
[41,42].

## Trial status

Recruitment of the participants started in September 2011. By 15 November 2012, 2,143 individuals had been assessed for eligibility and 266 had been randomized. Twenty-five individuals who completed baseline testing were found to have met T2D diagnostic criteria and were excluded from the study. It is anticipated that recruitment of participants will be end in February 2013.

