**Methods/design:**

We intend to recruit 796 participants for this open randomized clinical trial; 398 will be allocated to the intervention arm and 398 to the usual care arm. Several methods of recruitment will be used in order to maximize the number of participants. Individuals aged 50 to 75 years will be screened with a risk tool (AUSDRISK) to detect those at high risk of developing T2DM. Those with existing diabetes will be excluded. Intervention participants will undergo anthropometric and laboratory tests, and comprehensive surveys at baseline, following the fourth group session (approximately three months after the commencement of the intervention) and 12 months after commencement of the intervention, while control participants will undergo testing at baseline and 12 months only.

The intervention consists of an initial individual session followed by a series of five structured-group sessions. The first four group sessions will be carried out at two week intervals and the fifth session will occur eight months after the first group session. The intervention is based on the Health Action Process Approach (HAPA) model and sessions will empower and enable the participants to follow the five goals of the Life! program.

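### The article keeps a target of 796 and 80% power beside recruitment figures that project to about 313–334 randomized by its stated closing date

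*Protocol article*

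**What the plan says.** The Methods/design part of the abstract states the target as a current intention: "We intend to recruit 796 participants for this open randomized clinical trial". The section Sample size and power calculation derives it. The calculation is made "with a two-sided 5% significance level and 80% power", is based on the change in diastolic blood pressure in the earlier Greater Green Triangle project, and is "powered to detect an effect size of at least 0.23". On that basis "the total number required will be 598 (299 in each arm"). The next step is an inflation: "To allow for an estimated attrition of up to 25" per cent, "we require a total sample of 796 (398 in each arm"). The same section adds that this size is enough for total and HDL cholesterol, fasting plasma glucose, weight and waist circumference, because larger effects are expected for all of these. It gives no values for those effects.

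The section Trial status puts the start of recruitment in September 2011. It then reports: "By 15 November 2012, 2,143 individuals had been assessed for eligibility and 266 had been randomized". The closing statement is "It is anticipated that recruitment of participants will be end in February 2013". The article mentions no revised target, extension, planned acceleration or recalculated power.

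**The concern.** The target, the accrual to date and the closing date stand in the same article and do not fit together. After about 14 months one third of the target had been randomized (266/796 = 33%), and at most three and a half months remained. The article still offers 796 and 80% power as the description of the trial.

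The section Data analysis judges significance at P < 0.05, and the Discussion expects the results to inform policy and guidelines. If the trial closes on the stated date, a non-significant result for diastolic blood pressure could be read as coming from a trial with 80% power for the planned effect, when its power would be much lower. The assurance about the other risk factors is affected too. It rests only on their effects being larger than 0.23, and a smaller trial needs effects well above 0.23.

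**Working it through.** **Inputs.** From Sample size and power calculation: two-sided alpha 0.05, power 80%, standardized effect 0.23, 299 per arm evaluable, attrition up to 25%, 398 per arm randomized. From Trial status: start in September 2011, 266 randomized by 15 November 2012, end in February 2013. The days in September and February are not given, so the full range of each month is used.

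**1. The plan's own figures.**
- n per arm = 2 × (1.960 + 0.842)² / 0.23² = 297 (298 with the t distribution), against 299 stated.
- 598 / 0.75 = 798 after rounding up, against 796 stated.
- 796 × 0.75 / 2 = 298.5 per arm gives 80% power at 0.23.

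The plan's calculation therefore reproduces to within rounding.

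**2. Accrual to date.** From 1 or 30 September 2011 to 15 November 2012 is 441 or 412 days. With 30.44 days per month:
- 266 / 441 × 30.44 = 18.4 per month
- 266 / 412 × 30.44 = 19.7 per month

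**3. Projection at a constant rate.** From 15 November 2012 to 1 or 28 February 2013 is 78 or 105 days.
- Lowest: 266 + (266/441) × 78 = 313
- Highest: 266 + (266/412) × 105 = 334

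This is 39–42% of 796.

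**4. Rate needed to reach 796.** A further 796 − 266 = 530 would be needed.
- Over 105 days: 154 per month. Over 78 days: 207 per month.
- Relative to the observed rate: about 8 to 11 times.

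**5. Power and detectable effect at the projected size** (two-sample t test, alpha 0.05 two-sided; analysed per arm = N × (1 − attrition) / 2):

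| Attrition | Analysed per arm | Power at 0.23 | Effect detectable with 80% power |
|---|---|---|---|
| As planned (796, 25%) | 298.5 | 80% | 0.23 |
| 25%, N = 313–334 | 117–125 | 42–44% | 0.36–0.37 |
| None, N = 313–334 | 157–167 | 53–55% | 0.31–0.32 |

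By the normal approximation, 50% power at 0.23 needs 2 × 1.960² / 0.23² ≈ 145 per arm, or 290 analysed in total. At N = 313–334, power therefore falls below 50% once attrition exceeds about 7–13%.

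**6. Sensitivity to the constant rate.** With 25% attrition:
- Accrual doubled from 15 November 2012: N about 360–402, power about 47–51%.
- Accrual tripled: N about 407–469, power about 52–58%.

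**The case against.** The sample size calculation is correct, and a sample size section properly records the design as it was planned. Slow recruitment is a matter of conduct, and the article discloses it: any reader can set 266 against 796. The closing date is only anticipated. The projection is linear although accrual over time is not reported, and randomization follows screening and baseline testing, so the average rate includes a start-up period and the true total could be somewhat higher. The 25% attrition figure is a ceiling.

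Much of this stands. The 796 should not be overwritten, the range 313–334 depends on constant accrual, and 42–44% is the lower end of a range that runs up to 53–55%. None of it brings 796 within reach by February 2013, since even tripled accrual leaves power at 52–58% with the planned attrition. The shortfall is visible to a reader, but its consequence for power is not stated anywhere.

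Two stronger readings are tempting, and the article supports neither:
- A reader might infer that power is simply below 50%. That holds only if attrition exceeds roughly 7–13% of those randomized.
- A reader might infer that lipids, glucose, weight and waist circumference are equally underpowered. The figures above apply to an effect of 0.23, the value used for diastolic blood pressure. The article expects larger effects for the others without giving values, so their power cannot be computed; an outcome with a true effect of about 0.37 or more would still have 80% power.

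**Conclusion.** The concern holds as an inconsistency between the stated target and power on one side and the article's own accrual and closing date on the other. It is not an error in the sample size arithmetic. If recruitment closes in February 2013 and accrual stays near its average, about 40% of the target will be randomized. Power at 0.23 would then lie between about 42% and 55%, depending on attrition between 25% and none, instead of 80%. Besides constant accrual, this rests on the closing date being kept and on a simple two-group comparison of the kind that reproduces the plan's figure. For the other risk factors the conclusion is narrower: an effect merely larger than 0.23 no longer justifies the claim of sufficient power.

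**What to change.** Keep the 598/796 calculation as the design record and reconcile the abstract, Sample size and power calculation, and Trial status in one of two ways.

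- If recruitment will close in February 2013: add the expected final number (about 313–334 at constant accrual), the power at 0.23 (42–44% with 25% attrition, 53–55% with none) with the accrual and attrition assumptions stated, and the effect detectable with 80% power (0.36–0.37 or 0.31–0.32).
- If 796 is still intended: correct the February 2013 date to one that is consistent with the accrual expected.

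Unless 796 is reached, limit the statement on sufficient power to outcomes whose expected effect, given as a number, reaches the revised detectable size. For outcomes below it, state that a non-significant result will be interpreted through its confidence interval and not taken as evidence of no effect.

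The first route changes wording only and needs no extra participants; its price is that a stated figure becomes less favourable. The second needs more recruitment time: at the observed rate, 530 more participants would take about 27–29 months (530/19.7 to 530/18.4).

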## Abbreviations

AUSDRISK: Australian Type 2 Diabetes Risk Assessment; COAG: Council of Australian Governments; CVD: cardiovascular disease; DA Vic: Diabetes Australia Victoria; DPS: diabetes prevention study; FPG: fasting plasma glucose; GGT DPP: Greater Green Triangle Diabetes Prevention Project; GOAL: Good Ageing in Lahti Region; GP: general practitioner; HADS: Hospital Anxiety and Depression Scale; HAPA: Health Action Process Approach; MDPS: Melbourne Diabetes Prevention Study; OGTT: oral glucose tolerance test; T2DM: type 2 diabetes
